#### New training approach ‘ReHab-TOAT’

A new task-oriented arm training approach using a so-called remote handling concept, to generate haptic feedback on the patient’s arm, aiming at improvements on arm function level and, ultimately, on the level of activities and participation, was developed. This approach is called ReHab-TOAT—‘Remote Handling concept based, Task-Oriented Arm Training’. ReHab-TOAT may be applicable for a wide variety of patients with arm-hand problems due to a central nervous system deficit. However, as our Rehab-TOAT approach has yet to be evaluated on its effectiveness, we chose to focus specifically on patients in the chronic stage after a stroke, since these patients, in general, receive little therapy related to impaired arm function. Also, these patients are in a more stable phase after stroke, in which spontaneous recovery is minimal. Furthermore, since ReHab-TOAT’s effectiveness has not yet been established, providing such therapy to patients in the subacute stage, thus replacing other forms of therapy, in this stage of development, is ethically unacceptable.

ReHab-TOAT uses the principles of T-TOAT in combination with assistive forces to generate enriched haptic feedback. Furthermore, ReHab-TOAT uses strategies to improve self-efficacy and self-confidence to generalize and transfer training results to different contexts.

We hypothesize that:The use of haptic feedback during task-oriented training may lead to improvements of both arm function and arm skill performance in patients in the chronic stage after a stroke suffering from a moderately to severely affected arm.The quality of life of the patient will improve.The quality of life of the caregivers will improve as a result of a reduced need to support the patient in daily life tasks.These improvements will last beyond the training phase, because patients will continue to use their affected arm in daily life more, thus creating optimal conditions for generalization and transfer of ReHab-TOAT training effects towards other daily tasks performed in different contexts.Perceived usability of ReHab-TOAT is high, since the training approach and software are developed in co-creation with therapists, physicians and patients in order to meet their needs and expectations.

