### Objectives

The aim of this RCT is to investigate the effects of a 4-week ReHab-TOAT approach in addition to care as usual on improving arm function and arm-hand skill performance in chronic stroke patients with a moderately to severely affected arm-hand up to 9 months after training, compared to only care as usual. Furthermore, the aim of this study is to assess improvements in patients’ and their caregivers’ perceived quality of life, as well as the patients’ perception regarding the usability of the intervention, including both the developed approach and technology used.

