### Sample size

This sample size calculation [78] is based on data gathered in an earlier, small-sized pilot study, featuring pre- and post-intervention measurements, gauging the *order of magnitude* of any potential effect of the ReHab-TOAT treatment in a similar patient group, performed at the Adelante rehabilitation centre. Given the small sample and the skewed distribution, we used a log transformation on those data to estimate the group sizes needed for the RCT.

Given a log-transform of the skewed FMA data gathered during the aforementioned pilot study, a two-sided test and a:Mean (log-transformed) pre-intervention FMA value = 1.47 (sd = 0.12)Mean post-intervention FMA value = 1.65 (sd = 0.11)Power = 0.90Alpha = 0.01Loss-to-follow-up = 10%

fifteen patient-participants in each group, i.e. 30 participants in total, are needed.

Regarding the patients’ caregivers, 30 persons (associated with the aforementioned patients that are eligible and willing to participate) will also be asked to participate.

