### Statistical analysis

#### Primary study parameter(s)

Data from the primary outcome measure (FMA) will be tested for normal distribution using a Kolmogorov–Smirnov test. If normally distributed, data will be statistically analysed using a linear mixed model analysis (factors: GROUP and TIME). If, on the other hand, data are found to be skewed, a log transformation will be performed, after which a linear mixed model will be used to analyse the log-transformed data. Generally, alpha will be set at 0.05. In case of multiple comparison of the data post hoc, a Bonferroni approach will be used to avoid spurious potential false positive findings.

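### Holm would control the same error rate as the planned Bonferroni correction and never reject less when testing whether the benefit lasts to 9 months

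*Protocol article*

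**What the plan says.** The Objectives of the protocol article ask for the effect of ReHab-TOAT "up to 9 months after training, compared to only care as usual". The hypotheses under 'New training approach' add: "These improvements will last beyond the training phase". The FMA is measured at four baseline and four post-treatment visits (Table 2).

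Under 'Primary study parameter(s)' the FMA is analysed by a linear mixed model with group and time as factors. On the error rate the section says: "Generally, alpha will be set at 0.05". On multiplicity it says: "In case of multiple comparison of the data post hoc, a Bonferroni approach will be used to avoid spurious potential false positive findings". Five further outcomes (ARAT, MAL, EuroQol-5D, CarerQol and accelerometry) are analysed in the same way.

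The article does not list the comparisons that the correction covers. It is a condensed account, so that omission alone is not a finding. The method, however, is stated.

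**The concern.** A group-by-time model answers the durability question through contrasts at the follow-up visits, so the Bonferroni sentence probably governs the claim that benefit persists. The natural family is the four between-arm contrasts at T_FU, 3, 6 and 9 months, each tested at 0.05/4 = 0.0125.

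Bonferroni keeps that threshold for every contrast, even after some have been rejected. Holm orders the four p-values and compares them in turn with 0.0125, 0.0167, 0.025 and 0.05, stopping at the first failure. Its first threshold is Bonferroni's and the later ones are larger, so Holm rejects at least as much at any correlation and any effect size. With 30 patients, and a late effect that may be smaller than the early one, the difference can decide whether a real 9-month benefit is declared.

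**Working it through.** **1. The plan's own figure.** 'Sample size' gives log-FMA means of 1.47 (SD 0.12) before and 1.65 (SD 0.11) after treatment, "a two-sided test", alpha 0.01, power 0.90 and 10% loss.

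- Difference: 1.65 − 1.47 = 0.18. Root-mean-square SD: √((0.12² + 0.11²)/2) = 0.1151. Standardised effect: d = 0.18/0.1151 = 1.56.
- Normal formula: n = 2(2.576 + 1.282)²/1.564² = 12.2, so 13 per group. Then 13/0.90 = 14.4, so 15 per group. The stated 15 is reproduced.

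**2. Power for one contrast at the planned effect** (exact t-test, 13 evaluable per arm): 0.97 at alpha 0.05 and 0.89 at 0.0125. The trial was sized at alpha 0.01, which is already stricter than 0.0125.

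**3. Bonferroni against Holm, post-treatment scores only.** Simulation with 13 per arm, a two-sample t-test at each visit, four equally correlated visits and family alpha 0.05. The documents give no between-visit correlation, so 0.7 to 0.9 is assumed. Simulated figures are good to about one point.

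| True effect at T_FU / 3 / 6 / 9 months | Result | Bonferroni | Holm |
|---|---|---|---|
| 1.56 at every visit (planned) | 9-month power | 0.89 | 0.93–0.94 |
| 1.56 at every visit (planned) | all four visits significant | 0.76–0.81 | 0.90–0.92 |
| 1.56 / 1.2 / 1.0 / 0.8 (assumed decay) | 9-month power | about 0.28 | 0.44–0.46 |

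With all four nulls true, Bonferroni's actual family-wise error is 0.039, 0.033 and 0.026 at correlations 0.7, 0.8 and 0.9. Holm does not change this, because its first step is Bonferroni's. Its gain comes from the later steps, once one contrast has been rejected.

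**4. The same comparison with baseline adjustment.** Each visit is adjusted for the mean of the four baseline scores, as a stand-in for baseline-referenced contrasts from the mixed model. With equal correlation ρ between all visits, the squared correlation of a follow-up score with that mean is ρ²/((1 + 3ρ)/4). The residual SD is the square root of one minus this.

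| ρ | Squared correlation | Residual SD | Effective d for a raw 0.8 | 9-month power under the decay, Bonferroni → Holm |
|---|---|---|---|---|
| 0.7 | 0.49/0.775 = 0.63 | 0.61 | 1.32 | 0.72 → 0.88 |
| 0.8 | 0.64/0.85 = 0.75 | 0.50 | 1.61 | 0.89 → 0.97 |
| 0.9 | 0.81/0.925 = 0.88 | 0.35 | 2.27 | almost no gain; both near 1 |

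At the full planned effect every procedure is at or near 1, so the gain is negligible. At ρ = 0.8 the residual correlation between visits is only (0.80 − 0.753)/(1 − 0.753) = 0.19, and Bonferroni's family-wise error returns to about 0.047.

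**5. A fixed sequence as the alternative.** Testing in visit order at full alpha blocks the 9-month test if an earlier visit fails. If the effect instead builds up (40, 60, 80 and 100% of the planned effect; correlation 0.8; post-only t-tests), 9-month power is 89% under Bonferroni and about 32% under the fixed sequence.

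**The case against.** The strongest reply is that nothing here is wrong. Bonferroni is a standard, valid procedure, the article invokes it only for post hoc comparisons, and the four-contrast family is an inference. All of that stands, so the point can only be an improvement.

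A reader might go further and infer that the trial loses much of its ability to show a lasting benefit. The documents do not support that. Per-contrast power at the planned effect stays at 0.89 because the sizing used alpha 0.01. Large losses need a smaller late effect, which the documents do not give, and an analysis that ignores the baselines. For example, take a constant effect at 60% of plan and correlation 0.8. The chance of significance at all four visits is 22% under Bonferroni and 39% under Holm with post-only t-tests, but 89% and about 97% after baseline adjustment. Nor do the objectives require significance at all four visits.

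A reader might also take the family to be all 28 pairs of the eight visits and quote 68% power at 0.05/28 = 0.0018. The article specifies no such family. The 68% is also a between-arm power, whereas a within-arm visit pair is a paired comparison: at that threshold, with 13 patients and the planned effect, its power is 91% even at correlation 0.5.

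What the reply does not remove is that Holm makes the same guarantee under the same assumptions and is never worse. The planning effect is a pre-post change from a small pilot, meant to gauge an order of magnitude. It says nothing about 9 months, so protecting power against a fading effect is reasonable.

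**Conclusion.** The point holds as a free efficiency improvement and does not identify an error. That Holm is at least as powerful as Bonferroni, with the same family-wise error control, needs no assumption about correlation or effect.

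The size of the gain does need assumptions. At 9 months with unadjusted tests it is about 4 to 5 points at the planned effect and about 16 to 18 points under the assumed decay. With baseline adjustment the decay gain is 16 points at correlation 0.7, 8 points at 0.8 and almost nothing at 0.9. These figures rest on 13 evaluable patients per arm, equally correlated visits, the assumed decay and the inferred family of four contrasts. A fixed sequence is a trade-off and should not be the main proposal.

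**What to change.** In the multiplicity sentence, replace Bonferroni by Holm (Bonferroni–Holm) and name the family. Suggested text: 'For each outcome, the between-arm contrasts at T_FU, 3, 6 and 9 months form one family, tested with the Holm procedure at a family-wise two-sided alpha of 0.05. Baseline-to-baseline and within-arm visit comparisons are not part of this family.'

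The cost is one sentence, fixed before allocation is revealed for analysis. It needs no extra patients, visits or data, and no test result can become less favourable than under Bonferroni on the same four contrasts. The one practical loss is that simple simultaneous confidence intervals do not match Holm decisions as they match Bonferroni's. The report should therefore say whether its intervals are unadjusted or Bonferroni-adjusted.

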#### Secondary study parameter(s)

The data from the ARAT, the MAL the EuroQol-5D and the CarerQol will be statistically analysed similarly to the data of the FMA. The data regarding patients’ amount of arm-hand use during daytime, derived from the accelerometer signals (according to the protocols described by Lemmens et al. [66] and Franck et al. [38]), will also be statistically analysed similarly to the procedure used to analyse differences in the data of the FMA. Results from the SUS and the questionnaire on user experience of technology used will be reported descriptively. The single questions gauging for any event that may have influenced the patient’s or caregiver’s answer or measurement will only be used to identify/interpret any unexpected measurement and will be reported descriptively. The frequency and content of any additional therapy the participants received during the intervention period will be also reported.

#### Withdrawal of individual subjects, replacement and follow-up

Subjects can leave the study at any time for any reason if they wish to do so, without any consequences. The investigator can decide to withdraw a subject from the study for urgent medical reasons. In the group size calculation, a 10% drop-out rate has been used to compensate for subjects withdrawing from the study.

### Oversight and monitoring

This study (version: V2, dated July 6, 2021) has received ethical approval from the Medical Ethics Committee of Maxima Medical Centre in Veldhoven, the Netherlands (METC reference number: W21.003; CCMO code: NL76382.015.21). All amendments will be notified to the METC that gave a favourable opinion. All substantial amendments will be notified to the METC and to the competent authority. Non-substantial amendments will not be notified to the accredited METC and the competent authority, but will be recorded and filed by the sponsor.

A researcher external to the research team and without competing interest to this RCT is the monitor of the study. During three monitoring sessions, all items of the RCT will be checked following a strict monitoring plan and reported via a monitoring checklist. Additional comments for improvements will be provided by the monitor.

Serious and adverse events (SAE and AE) and potential effects will be reported by the coordinating researcher and the supervisor following a predefined protocol. The study investigator will report all SAEs to the sponsor without undue delay after obtaining knowledge of the events. The sponsor will report the SAEs through the web portal *ToetsingOnline* to the accredited METC that approved the protocol, within 7 days of first knowledge for SAEs that result in death or are life threatening followed by a period of maximum of 8 days to complete the initial preliminary report. All other SAEs will be reported within a period of maximum 15 days after the sponsor has first knowledge of the serious adverse events. All AEs will be followed until they have abated, or until a stable situation has been reached. Depending on the event, follow-up may require additional tests or medical procedures as indicated, and/or referral to the general physician or a medical specialist.

### Dissemination

Results of this RCT will be disseminated through scientific journal publications and conference presentations. Furthermore, the (general) results will be shared with all participants, as well as patient organizations. If the results of this RCT show that ReHab-TOAT is more effective in improving arm-hand function and arm-hand skill performance in chronic stroke patients, the results will be used to create a new arm-hand rehabilitation treatment protocol using remote-handling concepts for clinical implementation in rehabilitation centres. Furthermore, in case of a positive result, we would like to use the results to support the development of a similar yet less expensive, clinically more affordable medical device for the previously mentioned arm-hand rehabilitation treatment. Coded data will be made available to the scientific community upon request.

## Discussion

In this paper, we described the methodology of a randomized controlled single-blinded study that evaluates the effects of ReHab-TOAT on the performance at different levels of the ICF model of persons in the chronic stage after a stroke with an initially moderately to severely affected arm-hand, compared to care as usual.

In the present RCT, the focus lies on a patient subpopulation that is often excluded from research, i.e. on patients with a moderately to severely affected arm. Until recently, treatment options for these patients were limited [79], and even more so for such patients in the chronic stage after stroke. For the latter group, the aim in usual care is to maintain the current arm-hand function status and limit deterioration [10, 80]. However, more recent evidence has been showing that even years after stroke, patients may still gain improvements on a functional level, for example AHF, AHSP and quality as well as the amount of use of the affected arm in daily life [4, 36, 81–83]. The study of Timmermans et al. for example showed improvements of AHF and AHSP exceeding 10% improvement measured using the FMA, ARAT and MAL [20, 36]. If this RCT can underpin these results, the way we look at and organize treatment of patients in the chronic phase may change significantly with consequences for both amount and content of usual care for these patients.

### Methodological considerations

ReHab-TOAT has been developed in a co-creation process with companies, health care professionals, researchers and technicians to create a tailored training approach with suitable software, offering a high amount of possibilities for individualization of training based on the personal needs of the patient and the therapist. The whole development and research process of ReHab-TOAT has been done and described following well-known research protocols. First, the feasibility of ReHab-TOAT was explored in therapists and patients. Next, the order of magnitude of any potential effects in stroke patients was investigated. Subsequently, this RCT was designed and will be performed to investigate the effectiveness of ReHab-TOAT.

For a number of reasons, this study will start out with patients in the chronic stage after a stroke. First, it is assumed that these persons are stable regarding any spontaneous neurological recovery which only occurs in the first month(s) after stroke [84–86]. Any changes in AHF and/or AHSP status in the EXP group relative to baseline values and/or values from the CONTR group may therefore be attributable to the EXP intervention. One might argue that improvement in AHF and/or AHSP in the EXP group relative to the CONTR group may be caused by the amount of therapy provided to the former group. However, we consciously chose to compare our intervention to therapy as usual, because we want to compare it to real-life circumstances and not to any pre-construed circumstances without any knowledge on the effects of content and amount of therapy. Furthermore, there is no evidence that shows that a higher amount of therapy as usual in the chronic phase after stroke will result in substantial improvements. The authors are, however, aware that increased contact time alone, be it for training and/or measurements, may have a benefit on quality of life alone in chronic stroke patients, even without functional improvement of the arm-hand.

Moreover, we hypothesize that, next to AHF and AHSP, the motivation for training as well as the self-efficacy of the patient may increase to due improvements in daily life, which may lead to even higher improvements at function, activity and participation level as well as an increase in quality of life. Therefore, we chose to use measurements on different levels at the ICF model to evaluate the developed training approach in a real-life context.

Furthermore, we also involved the patient’s caregiver in this RCT, because it is known that improvements of the patient will reduce the time and effort the caregiver needs to support the patient in daily life [87]. In many trials, it is hypothesized that improvements of the patient have a positive influence on the caregiver, but there are only a few results due to the few existing measurements. Therefore, we decided to use a single question on the amount and content of provided care next to a worldwide known questionnaire for the QoL of the caregiver.

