### Trial design and timeline

This single-blinded RCT features two arms (EXP and CONTR). The EXP group will receive a 4-week ReHab-TOAT regime additional to any care the participants may receive outside the research context. The EXP group will also receive 1 additional session to familiarize themselves with the training system, prior to the start of the training phase. The CONTR group will not receive additional arm-hand therapy apart from care as usual at this stage, i.e. therapy participants already may receive from therapists in their current home situation. In our protocol, no restrictions will be imposed on any (additional) therapies participants currently receive.

In order to assess baseline stability, baseline measurements will be taken weekly during a period of 4 weeks. For both groups, follow-up measurements will be taken after the 4-week period in which the experimental group received ReHab-TOAT, as well as 3, 6 and 9 months thereafter. Figure 1 gives an overview on intervention and measurement time points.

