### Blinding

Blinding patients and/or therapists for treatment allocation is not possible. One trained researcher who is blinded for therapy modality will perform all measurements.

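### The Discussion accepts change from baseline in the EXP arm alone as attributable to ReHab-TOAT; only the EXP-minus-CONTR difference in change supports that

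*Protocol article*

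**What the plan says.** Under Methodological considerations the article explains why it starts with chronic patients: "it is assumed that these persons are stable regarding any spontaneous neurological recovery which only occurs in the first month(s) after stroke". It then concludes, of the experimental intervention: "Any changes in AHF and/or AHSP status in the EXP group relative to baseline values and/or values from the CONTR group may therefore be attributable".

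Other sections bear on that inference:

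- Objectives sets a between-arm question: the effect of ReHab-TOAT added to usual care, "compared to only care as usual".
- Primary study parameter(s) states: "data will be statistically analysed using a linear mixed model analysis (factors: GROUP and TIME". It names no contrast, and it provides for Bonferroni-adjusted post hoc comparisons.
- Trial design and timeline: "In order to assess baseline stability, baseline measurements will be taken weekly during a period of 4 weeks". Table 2 shows FMA, ARAT and MAL at four baseline and four later visits, eight in all. Accelerometry and EuroQol-5D have one baseline.
- The same section says that "no restrictions will be imposed on any (additional) therapies participants currently receive". This therapy is recorded at each measurement session and reported.
- Discussion, on chronic patients with a moderately to severely affected arm: "the aim in usual care is to maintain the current arm-hand function status and limit deterioration".
- Blinding: "Blinding patients and/or therapists for treatment allocation is not possible". One blinded researcher performs all measurements.

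**The concern.** Joined by *and/or*, the two comparisons become alternatives: a change from baseline in EXP would suffice without reference to CONTR. The premise excludes one cause of change, spontaneous recovery, and leaves others that the article itself describes. Familiarity with the tests can raise FMA, ARAT and MAL over eight sittings. Outside therapy continues without limit. Usual care that aims to limit deterioration implies that a flat course over about 11 months (4 weeks of baseline, 4 weeks of treatment, 9 months of follow-up) is not assured.

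What is at stake is the conclusion that the report may draw. A movement common to both arms could be presented as an effect of the training. Under Dissemination, a favourable result would feed into a new treatment protocol and further device development.

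**Working it through.** **1. The plan's own figure.** Sample size gives log-transformed FMA means of 1.47 (SD 0.12) before and 1.65 (SD 0.11) after the intervention, two-sided alpha 0.01, power 0.90 and 10% loss.

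- Difference: 1.65 − 1.47 = 0.18.
- Pooled SD: √((0.12² + 0.11²)/2) = 0.1151.
- Per arm: n = 2 × (2.576 + 1.282)² × 0.1151² / 0.18² = 12.2, so 13.
- After 10% loss: 13/0.90 = 14.4, so 15 per arm and 30 in total.

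The stated figure is reproduced. (A t-based calculation gives 14, or 16 after loss.) It is reached by using the pilot's pre-post change as the between-arm difference, that is, with no change in CONTR. This is the same line of thought as the Discussion sentence. It is a separate matter, however, and does not show that the sentence governs the analysis.

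**2. Does the conclusion follow from the premise?**

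| Influence | Basis in the article | Excluded by the premise? | Removed by comparison with CONTR? |
|---|---|---|---|
| Spontaneous recovery | Methodological considerations | Yes | Yes |
| Repeated testing | Table 2, eight assessments | No | Yes, if shared |
| Background outside therapy | Trial design and timeline | No | Only if balanced |
| Deterioration | Discussion | No | Yes, if shared |
| Expectation | Blinding | No | No |

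The premise settles the first row only. Deterioration would hide a gain within EXP and not create one, but it still biases within-arm change, and only CONTR can show its size.

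**3. Illustration of size.** From the document: SDs 0.12 and 0.11, n = 15, alpha 0.05 two-sided (Primary study parameter(s)). Assumed, with no figure in the document:

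- no treatment effect;
- a drift shared by both arms of 0.02 or 0.04 on the log10 scale (10^0.02 = 1.047, about 5%; 10^0.04 = 1.096, about 10%);
- pre-post correlation r of 0.7 to 0.9;
- log base 10.

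SD of change = √(0.12² + 0.11² − 2r × 0.12 × 0.11). The noncentrality parameter is drift × √15 / SD of change, with 14 degrees of freedom and critical t = 2.145.

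| r | SD of change | Significant within EXP, drift 0.02 | Significant within EXP, drift 0.04 |
|---|---|---|---|
| 0.7 | 0.090 | 13% | 36% |
| 0.8 | 0.073 | 17% | 50% |
| 0.9 | 0.052 | 28% | 79% |

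With 13 evaluable patients the ranges are about 11 to 25% (drift 0.02) and 32 to 72% (drift 0.04). At r = 0.5 and n = 15 the figures are 10% and 24%. A between-arm test of change stays at 5% throughout, because a drift equal in both arms cancels.

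**The case against.** The sentence stands in the Discussion, justifies the choice of population and is hedged with *may*. Nothing in the article says that success will be declared on within-EXP change. Objectives, Dissemination and the opening of the Discussion all frame the question against usual care, and the model includes GROUP. The four baselines can expose a practice trend, the assessor is blinded, and outside therapy is recorded. The illustration uses a two-point paired test, whereas the plan is a mixed model.

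Most of this stands and limits the point. A reader might infer that the primary analysis is a within-arm test; the documents do not support that. The model description does not exclude a within-arm reading either, but leaving the exact contrast to an analysis plan is normal and is not criticised here. The baselines can show a trend for FMA, ARAT and MAL only before treatment, not drift during treatment or over the following 9 months.

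A reader might also infer that an EXP arm back at its baseline at 9 months would be declared a lost effect even if CONTR had declined. That would require a baseline-only rule. Under *and/or*, the comparison with CONTR would still show the effect.

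Nor does the control arm remove every rival explanation. CONTR receives no added therapy and patients know their allocation, so expectation can differ between arms, and so can outside therapy taken up during the trial.

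**Conclusion.** The point holds as a fault in a stated inference. The article's own account of what may be attributed to ReHab-TOAT is wider than its objective, and its premise does not carry it. The planned analysis is not shown to be wrong. The 13 to 79% range shows how readily a shared drift could pass as an effect in a simple within-arm test. It rests on the assumed drift and correlation, and it is not an error rate of the mixed model. The 5% for the between-arm comparison likewise assumes drift equal in both arms. The wording should be corrected, because it bears on what the trial may conclude and the correction is trivial.

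**What to change.** 1. In Methodological considerations, delete *baseline values and/or*, so that the changes in EXP are judged only relative to values from the CONTR group.
2. State that attribution, immediately after the intervention and at 3, 6 and 9 months, rests on the EXP-minus-CONTR difference in change from baseline, which is the GROUP-by-TIME contrast at that visit in the planned mixed model.
3. Report within-arm changes descriptively.
4. Add one sentence saying that this comparison removes influences shared by both arms, but not expectation or differences in outside therapy between the arms.

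The cost is a few lines of protocol wording and a matching reporting rule. No new data, visits or patients are needed, and the sample size is unaffected.
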